##### Step 3: Analyzing the Information

The aim is to identify problems in the system that may have contributed to maternal death, stillbirths, and neonatal deaths, especially those that could have been averted. Data analysis will include quantitative components, such as identification of trends in rates and causes of death and geographic location. Qualitative analysis will provide additional insight into the problems that caused the deaths of individual cases and more general information about groups of deaths caused by similar contributing factors. The use of both types of data together will provide a more robust analysis of the problems and aid the audit committee to identify priorities for action.

##### Step 4: Recommending Solutions

The aim of this critical step is to find ways to move from problems to action by identifying specific, measurable, attainable, relevant, and time-bound solutions. A formal platform will be created to present the findings of the audit process. The moderator will guide the discussion and present aggregated data and trends in addition to selected individual cases presented anonymously without bias. It is recommended that no more than 2 cases per 2-hour session shall be reviewed per month. After the presentation of the case summary, the main facts are analyzed by the audit members. Discussion will follow the presentation, reflecting on the modifiable factors of specific cases and any changes in trends from meeting to meeting.

A systematic and exhaustive analysis of the case should be conducted to effectively understand the chain of events related to the case. After identifying the main problems at the various steps described previously, the audit committee is invited to discuss and make the case for why a procedure or an act should be considered adequate or inadequate, by referring to the established standards of practice. Dysfunctions and their causes should be prioritized, and energy should be devoted to solving the most significant problems and those for which the implementation of a solution is feasible. Then, the committee will investigate what its causes and related factors may be, and these can be related to (1) personnel: qualification, skills, availability, attitude, and so on; (2) drugs, supplies, and equipment: availability, accessibility, and so on; (3) protocols: availability, knowledge, understanding, use, and so on; (4) management or care organization: coordination, communication, and so on; and (5) patient and his family: financial accessibility, misunderstanding, willingness, and so on. Final step will be the identification of cause of morbidity or death by (1) reviewing the medical cause of severe morbidity or death and identifying the various factors or events that may have contributed to the outcome, (2) comparing the cause of the morbidity or death documented in the patient’s record with the audit committee findings, and (3) determining whether the death was preventable.

Following the abovementioned steps in analyzing the case, the moderator leads the discussion to select the problems to be solved in order of priority. Problems must be prioritized based on the significance of their effect on prognosis and the feasibility of the actions necessary to solve them. Through the moderator, the audit committee will then reach a consensus on appropriate, evidence-based strategies to address the main gaps at the health facility level (phase-3 delay). The solutions will balance the priorities based on burden and feasibility and may be related to ongoing or one-off activities.

In addition to possible solutions at the health care facility level, the audit committee in the community will identify cases that are closely linked to the community and agree on select cases to present during the postaudit community feedback meeting. Community-level solutions will be directly related to phase-1 and phase-2 delays. The audit committee will ensure that findings are shared in the appropriate forum and work with the community to develop solutions that are clear, attainable, and straightforward about the potential for improving care, without placing blame.

Recommending realistic solutions to reduce the factors associated with maternal, perinatal, and neonatal morbidity and mortality in the community can be challenging. Careful considerations regarding the capacity of the community to implement the recommendation and the method of communication will be prioritized. The 2016 WHO guidelines for audit and review of stillbirths and neonatal deaths advises formulating a recommendation in collaboration with community leaders empowered to make the recommended change to ensure it is effective. To alleviate the risk of developing distrust between the community and the health system, recommendations will not be “handed down” from the health facility audit committee but rather discussed as a partnership with the community. In addition, effective communication, relayed consistently and sensitively, will be developed through the early selection of appropriate community representatives to participate in the audit meetings. Through the deliberate selection of key community representatives, efforts will be made to encourage an open, synergetic, and nonjudgmental forum between the community and health facility to ensure that the chosen recommendation is attainable and will ultimately strengthen the community voice.

Our data suggest that the process of fostering active partnerships between health care providers and community members through dialogue, planning, and collective action by learning from what went wrong and emerging lessons can improve community trust and quality of care [21].

##### Step 5: Implementing Changes

The aim is to take immediate, medium-term, or long-term actions to prevent maternal deaths, stillbirths, and neonatal deaths, using successes to advocate for and spur further action. Implementing changes is the primary objective of the audit cycle. To be more effective, the audit committees will focus on the modifiable factors that are within the control of health workers and the community.

The findings of the audits will be shared with the concerned authorities in health facilities, program managers, and community representatives to spur policy and practice related change. DHO will be onboard to ensure that the decisions agreed upon are implemented at the facility and community levels. The decisions proposed by the audit committee and endorsed by DHO will be implemented to address the bottlenecks at the demand side (delay in care and financial and mobility challenges) and the supply side (lack of hospital supplies, staff, and resources).

##### Step 6: Monitoring and Evaluation

In addition to the monthly audits, the project committee will also collect administrative and survey data to capture the process and outcome indicators. From independent, third-party surveys and data sources such as DHIS, facility registers, and LHW management information system, the impact of the intervention will be evaluated based on the maternal perinatal and neonatal mortality and morbidity outcomes and rated for all pregnant women, mothers, and newborns.

The model will contain audit guidelines, protocols, and training materials and tools for effective monitoring at the facility level in the targeted districts with their respective catchment populations. A monthly monitoring cycle will be set up within the implementing facilities to ensure effective implementation of the audit systems.

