### Primary Outcomes

The primary outcomes include the following:

Proportion of facilities initiated to implement an audit system for measuring the adoption of audit system,Proportion of audit committees with community representation and proportion of committee audit members sharing feedback regularly to measure the feasibility of the audit system, andQualitative narrative approach for acceptability and exploring the facilitators of and challenges in implementing audit systems.

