### Secondary Outcomes

The secondary outcomes include the following:

Geographic distribution of mortality to measure the percentage coverage or reach in the implementation district,Change in trends in data recording and reporting to measure effectiveness,Categorization of mortality and maternal near-miss cases among Three Delays framework,Number of awareness sessions covering the proportion of the catchment population,Number of referrals in and out of the health facility,Number of transport mechanisms linked to health facilities by audit committee members, andProportion of health facilities implementing actionable recommended actions at the facility level.

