### Data Management and Analysis

The data collection tool will be developed in English and then translated into the local language to be administered to the local community visiting the health facilities. Data will be collected manually and entered through a specifically designed application. The application will be installed on laptop or desktop at each health facility under the supervision of project leadership. The Aga Khan University Data Management Unit will develop an electronic database that includes the filters and data quality check indicators. Data will be entered at the end of every week and uploaded onto the Aga Khan University Data Management Unit server. All data files will be stored for 5 to 7 years and then deleted according to organizational procedures for the permanent destruction of electronic and paper data.

Descriptive statistics will be used to estimate maternal, neonatal, and other key quantitative variables. The Three Delays framework will be used to categorize the identified modifiable factors. Action reports will be submitted based on the recommendations proposed by the audit committee. The data will be analyzed using Stata (version 16; StataCorp) and NVivo (Lumivero) software and password-protected Excel (Microsoft Corp) files. A unique code identifier will be assigned for the cases to be selected for discussion in audit meetings. The village name and health facility name will be kept confidential in audit meetings and, instead, codes will be used. In addition, regular meetings, planned dissemination of study findings including manuscript publication, stakeholder knowledge sharing workshop including community participation, and conference presentations will be conducted.

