### Limitations

Our project is unique with its focus on community engagement and representation integrated into the facility-based audit system. As such, it has strong implications for scale-up and uptake across Pakistan’s regional districts. Nevertheless, the primary limitation of this study is the recording of neonatal and maternal deaths and their complete medical history from health facilities. To overcome this challenge, there will be planned quarterly refresher training for the facility staff regarding source register apprising and DHIS. Moreover, in monthly audit cycles, the cases will be presented by audit committee members including community representatives. This will help support local ownership for facilitating and using existing resources. DHOs will ensure the presence, retention, and participating attitude of audit committee members. The implementation design includes quantitative and qualitative approaches, which can provide strong evidence for the impact generated by the audit system implementation.

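### The protocol promises an evaluation of impact on mortality and morbidity, and strong evidence of impact, but lists no such outcome, and the design as described cannot separate fewer deaths from changed reporting

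*Protocol article*

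**What the plan says.** Step 6 (Monitoring and Evaluation) states that "the impact of the intervention will be evaluated based on the maternal perinatal and neonatal mortality and morbidity outcomes". The information is to come "From independent, third-party surveys and data sources such as DHIS, facility registers, and LHW management information system". Limitations adds that the quantitative and qualitative approaches together "can provide strong evidence for the impact generated by the audit system implementation".

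The outcome lists point elsewhere:

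- **Primary Outcomes.** Adoption is the "Proportion of facilities initiated to implement an audit system for measuring the adoption of audit system". Feasibility is the "Proportion of audit committees with community representation and proportion of committee audit members sharing feedback regularly". Acceptability is qualitative.
- **Secondary Outcomes.** Mortality is mentioned twice: as a geographic distribution that measures reach, and as a sorting of cases by the Three Delays framework. The item tied to effectiveness is "Change in trends in data recording and reporting to measure effectiveness".
- **Abstract, Methods.** Effectiveness covers recording and reporting trends and also the modifiable factors identified for mortality and morbidity.
- **Research questions (History of Perinatal Audit Systems in Pakistan).** The four questions concern feasibility, reporting of deaths and near misses, identification of factors with follow-through on recommendations, and early referral.
- **Data Management and Analysis.** "Descriptive statistics will be used to estimate maternal, neonatal, and other key quantitative variables".
- **Study Setting.** One district. No control area or baseline period is stated.

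**The concern.** The document uses two different yardsticks. Its outcome lists and research questions judge the project on adoption, feasibility, reporting, delays and actions taken. Step 6 judges its impact on deaths and severe morbidity. Limitations then rates the evidence for impact as potentially strong.

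This matters because the results are meant to inform scale-up. A reader who takes Step 6 and Limitations together would expect the study to show whether the audit lowers mortality. A one-district descriptive study with no stated comparator does not have that property. There is also a specific obstacle: the intervention is designed to change how completely deaths are recorded. A rise in recorded deaths could be a success of the audit, and a flat or falling count could reflect effect, ascertainment or background trend.

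**Working it through.** The protocol states no effect estimate, event target or completeness figure for this evaluation, so there is no figure of its own to reproduce. The check has two parts.

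**1. Setting the sections side by side**

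| Section | What is measured | A mortality or near-miss rate, or a change in one? |
|---|---|---|
| Primary Outcomes | adoption, feasibility, acceptability | no |
| Secondary Outcomes, geographic distribution | reach | no |
| Secondary Outcomes, Three Delays | classification of cases | no |
| Secondary Outcomes, effectiveness item | recording and reporting trends | no |
| Abstract, effectiveness | reporting trends, modifiable factors | no |
| Four research questions | feasibility, reporting, factors and actions, referral | no |
| Step 6 | impact on mortality and morbidity | yes |

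Step 3 of the audit cycle does mention trends in death rates. That text describes how a committee analyses its cases to set priorities. It is not an evaluation of impact.

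**2. What a change in recorded deaths would mean**

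The Introduction says the DHIS seldom records mortality consistently and reliably. The second research question asks whether the audits improve reporting of deaths and near misses at DHIS facilities. Limitations plans quarterly refresher training on the source register and DHIS, and Step 1 arranges monthly community reporting by LHWs or CMWs. The DHIS, facility registers and the LHW system are all among the sources that Step 6 names.

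Let c0 and c1 be the share of deaths captured before and after the audit takes hold. With births counted equally well in both periods,

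observed rate ratio = true rate ratio × (c1 / c0).

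The true ratios are 0.70, matching the 30% perinatal reduction cited in the Introduction, and 1.00 for no change. The completeness values are assumptions, because the protocol gives none.

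| Assumed completeness, before to after | c1 / c0 | Observed if true ratio is 0.70 | Observed if no true change |
|---|---|---|---|
| constant | 1.00 | 0.70 | 1.00 |
| 80% to 90% | 1.125 | 0.79 | 1.125 |
| 50% to 70% | 1.40 | 0.98 | 1.40 |
| 60% to 90% | 1.50 | 1.05 | 1.50 |

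With a true 30% fall, the observed ratio stays below 1 only while c1 / c0 is below 1 / 0.70 = 1.43. Completeness may change by different amounts in different sources, so one true effect can look like a fall in one source and a rise in another.

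**The case against.** The strongest reply is that this is a feasibility study and largely says so. The hypothesis, the primary objectives and the Conclusions all speak of feasibility and potential scale-up. The sentence in Limitations says only that the approaches can provide such evidence and does not mention mortality; impact there could mean reporting, referrals or recommendations carried out. This has force as to tone. It does not remove the mismatch, because Step 6 is where the document says what impact will be evaluated on, and it names mortality and morbidity.

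A second reply is that independent surveys are among the sources and may not share the reporting change. That is possible, but the article ties no source to any outcome. A survey with constant ascertainment would still leave one district without a stated comparator.

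A third reply is that a condensed article leaves models and source hierarchies to a full protocol or SAP. That is accepted, and their absence is not held against it. The point rests on what the article states: outcome lists that disagree with Step 6, and a claim about strength of evidence.

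Two stronger readings are tempting and are not supported:

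- A reader might infer that several outcomes in several sources create a multiple-testing problem, with a confirmatory conclusion drawn from whichever moved favourably. The document plans no test or significance level, lists the sources jointly, and describes frequencies, percentages and triangulation. False-positive rates would describe a procedure nobody has proposed.
- A reader might infer that the study is underpowered for maternal deaths or adequate for neonatal deaths. Either needs a comparison window with complete capture, which the document does not state.

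**Conclusion.** The point holds as an inconsistency and an overstated property. Step 6 evaluates impact on outcomes that appear in none of the outcome lists or research questions, and Limitations describes the evidence for impact as potentially strong. In a single district, analysed descriptively and with no stated control or baseline period, a change in recorded deaths cannot be attributed to the audit.

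The possible distortion is large enough to reverse direction. Under the assumed rise in completeness from 60% to 90%, a real 30% reduction would look like a 5% increase. Under 80% to 90%, it would look like a reduction of about 21%. These sizes rest on the assumed completeness values and on equal counting of births. The textual mismatch depends on none of them.

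The feasibility, adoption and reporting aims are not affected.

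**What to change.** Three changes of wording would bring the sections into line:

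1. **Step 6.** State that mortality and near-miss figures are exploratory and descriptive, that they will be reported for every outcome and every source with 95% CIs and alongside the completeness of reporting, and that no claim of impact on mortality will be based on them.
2. **Secondary Outcomes.** Add these measures under an exploratory label, so that the list and Step 6 agree.
3. **Limitations.** Confine the statement that the design "can provide strong evidence for the impact generated by the audit system implementation" to feasibility, adoption and reporting.

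No new data are needed, since recording and reporting trends are already a secondary outcome. The cost is a less favourable stated claim about impact.

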The District Health Information System (DHIS) seldom records and reports mortality (eg, maternal mortality and neonatal mortality) and severe morbidity indicators consistently and reliably (eg, birth asphyxia and preeclampsia), leading to challenges in data completeness in capturing vital statistics through routine health and administrative data. Audit systems at the facility levels can provide for sustained improvements in the quality of provision and delivery of services. Community linkages and engagement ensure proactive and detailed discussion of the causes and modifiable factors leading to the deaths, essential for improved working relationships between community members, health providers, and policy makers [11]. Audits of stillbirths and neonates also contribute to achieving Every Newborn Action Plan goal for reducing stillbirths and neonatal deaths to <12 newborn deaths per 1000 live births [12].

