### History of Perinatal Audit Systems in Pakistan

Previous efforts to introduce facility audit systems by the Pakistan Ministry of National Health Services, Regulations, and Coordination have used the phased implementation of the Maternal and Perinatal Death Surveillance and Response to enhance reporting, recording, tracking, and auditing of deaths [17]. The World Health Organization (WHO) is currently assisting Khyber Pakhtunkhwa and Baluchistan provinces, and United Nations International Children’s Emergency Fund (UNICEF) is helping the Sindh province in implementing audit mechanisms, but results have not been made public. The United Nations brief on COVID-19 [18] and the Pakistan Health Report 2020 [19] have stated that the Maternal and Perinatal Death Surveillance and Response has great potential for success.

We hypothesize that a WHO audit cycle that is locally acceptable in close consultation with local community representatives and health care providers is feasible for implementing a robust audit system in rural settings. Specifically, we asked the following questions:

Is the implementation of facility-based maternal and perinatal mortality audits in combination with targeted community engagement feasible in rural Pakistan?Will the maternal and perinatal audits improve the reporting of deaths and maternal near misses at the DHIS health facilities?Will the audit systems help better identify medical and nonmedical factors of deaths and near misses, and how doable recommendations are implemented through integration of feedback loops within the health facilities and communities?Will the community-facility audit interaction improve the early referral proportions?

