**Maternal *near miss***
Maternal *near miss* is a situation in which a pregnant woman nearly dies but survives a complication that occurred during pregnancy, during childbirth, or within 42 days of the termination of pregnancy. It can involve severe pregnancy-related complications (severe postpartum hemorrhage, severe pre-eclampsia, eclampsia, sepsis, and ruptured uterus) or critical interventions (blood transfusion, laparotomy, admission to an intensive care unit, hysterectomy, and other emergency surgical interventions in the abdominal cavity).

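### Step 6 judges impact on mortality and morbidity partly from registers whose reporting the audit is meant to raise, with no stated way to separate reporting gain from true change

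*Protocol article*

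**What the plan says.** All references are to the protocol article.

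- **Step 6: Monitoring and Evaluation** names the sources, "From independent, third-party surveys and data sources such as DHIS, facility registers, and LHW management information system", and says that from them "the impact of the intervention will be evaluated based on the maternal perinatal and neonatal mortality and morbidity outcomes". It ranks no source above another.
- **Background** says that DHIS "seldom records and reports mortality (eg, maternal mortality and neonatal mortality) and severe morbidity indicators consistently and reliably".
- **The research questions** (end of History of Perinatal Audit Systems in Pakistan) ask: "Will the maternal and perinatal audits improve the reporting of deaths and maternal near misses at the DHIS health facilities"?
- **Secondary Outcomes** include "Change in trends in data recording and reporting to measure effectiveness". No mortality or near-miss rate is listed there or under Primary Outcomes.
- **Steps 1 and 2** of the audit cycle build in measures to capture every death and to link community deaths to the facility audit. **Limitations** adds quarterly refresher training on source registers and DHIS.
- **Study Setting** names one district and describes no comparison area. **Data Management and Analysis** specifies descriptive statistics.
- **Limitations** closes by saying that the design has quantitative and qualitative approaches, "which can provide strong evidence for the impact generated by the audit system implementation".

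**The concern.** The intervention changes the instrument that measures its effect. If the audit works as intended, a larger share of deaths and near misses reaches DHIS and the facility and LHW records. Under Secondary Outcomes that rise counts as effectiveness. Under Step 6 the same rise, read as a mortality or morbidity outcome, looks like failure.

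The article names incomplete recording of deaths as its primary limitation. Its remedy includes register and DHIS training, which improves the data but also widens the gap in capture between early and late periods.

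The study is meant to inform scale-up. A district office that sees recorded deaths rise could conclude that the audit did harm or nothing, when reporting had improved and mortality had fallen. Nothing stated in the article would let it tell these apart.

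**Working it through.** The article states no completeness figure, event count or power calculation, so there is no figure of its own to reproduce. The check is whether a plausible gain in reporting is large enough to matter against effects of the size that the article cites.

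**Inputs from Background**
- Inpatient maternal mortality: adjusted odds ratio 0.85.
- Inpatient neonatal mortality: adjusted odds ratio 0.74.
- Perinatal mortality: 30% reduction (95% CI 21% to 38%), that is, a ratio of 0.70 (0.79 to 0.62).
- Neonatal mortality: 41 per 1000.

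**Assumptions**
- The two odds ratios are treated as rate ratios.
- Capture means the completeness of recorded deaths relative to recorded births. If births became more complete by the same factor, the rate ratio would not move.
- Capture before and after is assumed, because the article gives neither.

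**Formula**

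Observed ratio = true ratio × (capture after ÷ capture before).

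The fall disappears when the capture ratio reaches 1 ÷ true ratio.

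**Break-even rise in capture**
- Maternal: 1 ÷ 0.85 = 1.18
- Neonatal: 1 ÷ 0.74 = 1.35
- Perinatal: 1 ÷ 0.70 = 1.43 (1 ÷ 0.79 = 1.27 to 1 ÷ 0.62 = 1.61 over the interval)

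**Observed ratio under assumed capture**

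| Capture before → after | Capture ratio | True 0.85 | True 0.74 | True 0.70 |
|---|---|---|---|---|
| 50% → 80% | 1.60 | 1.36 | 1.18 | 1.12 |
| 50% → 70% | 1.40 | 1.19 | 1.04 | 0.98 |
| 60% → 90% | 1.50 | 1.28 | 1.11 | 1.05 |
| 70% → 80% | 1.14 | 0.97 | 0.85 | 0.80 |
| 80% → 90% | 1.125 | 0.96 | 0.83 | 0.79 |

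In rates, for the first row: a true neonatal rate falling from 41 to 41 × 0.74 = 30.3 per 1000 would be recorded as 41 × 0.50 = 20.5 rising to 30.3 × 0.80 = 24.3 per 1000.

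**Where reversal stops.** From an 80% baseline the 0.74 effect would need 0.80 × 1.35 = 108% capture to cancel, and the 0.70 effect 0.80 × 1.43 = 114%. Neither is possible, so from that baseline these effects can be understated but not reversed.

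The article cites no effect on near misses, so no arithmetic is offered for them. The mechanism is the same, since the research question covers their reporting too.

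**The case against.** **The surveys come first in the sentence.** A reader might infer that impact rests only on the registers that the audit alters. The text does not support that, because Step 6 opens with independent third-party surveys. This limits the point to part of the evidence. It does not remove it: the sentence pools the sources, and nothing says that the surveys decide or calibrate the registers.

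**Mortality is not a listed outcome.** The primary outcomes are adoption, feasibility and acceptability, and effectiveness is already defined through recording and reporting trends. This stands, and it is why the point is not graver. A reader who infers that the study's main results are compromised goes too far.

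**Reversal is not certain.** A reader might infer that a successful audit will look harmful. That depends on baseline capture, which is not stated. In the last two rows of the table no effect is reversed.

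**Source precedence belongs in an analysis plan.** Detail does. But the article itself fixes the impact measure, the sources and the strength of the claim, and those statements conflict with its own account of the registers.

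**The limitation is acknowledged.** Limitations does name the recording of deaths, and says that the design can, not will, give strong evidence. It does not connect improved recording with the reading of mortality trends.

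**Near misses might carry a second artefact.** The definition admits "critical interventions (blood transfusion, laparotomy, admission to an intensive care unit, hysterectomy, and other emergency surgical interventions in the abdominal cavity", and Step 5 aims to relieve "the supply side (lack of hospital supplies, staff, and resources". A reader might infer that better access alone will push the count up. The documents do not say that transfusion, surgical or intensive care capacity will expand, and the listed near-miss outcome is a categorisation by delay, not a rate. The point does not rely on this. It does not rely on the precision of a maternal mortality comparison either, which would need an assumed birth rate and a pre-period that the article does not describe.

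**Conclusion.** The concern holds in limited form. Step 6 judges impact on mortality and morbidity partly from records that the intervention is designed to make more complete, and the article gives no means of separating reporting gain from true change. Whenever capture of deaths rises relative to births, a register-based trend is biased towards apparent harm. The bias ranges from modest understatement (true 0.74 seen as 0.85 at 70% to 80%) to reversal (seen as 1.18 at 50% to 80%). These figures rest on assumed capture levels and on reading odds ratios as rate ratios; the direction of the bias does not. The unreliability statement is about DHIS; the article makes no such statement about the LHW system.

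Strong evidence of impact is therefore not something that one district with no described comparator and a descriptive analysis can deliver from these sources. The primary feasibility outcomes and the listed reporting outcome are unaffected. This should be fixed, but it does not undermine the study's main purpose.

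**What to change.** 1. **Step 6.** Report register deaths and near misses as a reporting and completeness outcome, in line with Secondary Outcomes, and state that their change will not be interpreted as impact on mortality or morbidity.
2. **Any mortality trend.** Show it only from the independent survey source, and only if the survey's case-finding is unchanged over time. Put register-to-survey completeness beside it and label it descriptive. The condition matters because the article does not describe the survey's method or baseline. If it is not met, show no mortality trend as impact.
3. **Limitations.** Replace the closing claim ("which can provide strong evidence for the impact generated by the audit system implementation") with evidence on feasibility, reporting completeness and identified modifiable factors.

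The cost is wording in two sections, one extra tabulation and a more modest claim.
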